## Patient Recruitment

### Sample Size

We have powered this trial to detect an effect size of 0.4. Our effect size is towards the conservative end of our platform trial confidence interval [19] SMD: 0.63; 95% CI 0.18 to 1.07, an effect size achieved by Pilling et al [22] SMD 0.42; 95% CI -0.05 to +0.89, and in line with the findings of recent reviews [23] and our group's recent meta regression [14]. An effect size of 0.4 is also regarded as the most reasonable for determining differences between interventions that are clinically meaningful [24]. Such an effect size at 90% power (alpha 0.05) would require 132 patients per group in a two armed patient randomised trial. For the proposed cluster trial, with 14 patients per cluster and the ICC found in our trial platform of 0.06, the design effect would be 1.65. The cluster trial sample size is, therefore, 440. In order to follow up 440 patients, we will recruit and randomise 550 patients to anticipate a loss to follow up of 20%.

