## Analysis

### Statistical analysis of clinical data

We will analyse our primary outcome of severity of depression on the PHQ-9 at four months using between groups analysis of covariance on individual baseline depression score. Analysis will take clustering into account by use of robust standard errors in Stata. All other clinical outcome variables will be analysed as secondary variables in the same way, using least squares or ordered logistic regression as appropriate. We will analyse outcomes by site variables to detect any effects on treatment outcomes of a 'therapist effect' - differences between case managers - and practice level variables. We will investigate the effects of any missing data using imputation by best subset regression and apply CONSORT standards for cluster randomised trials [37] in data reporting.

The incremental cost per QALY of the intervention compared to the control will be calculated from NHS and Personal Social Services (PSS) perspectives following NICE evaluation guidance [38] and a wider societal perspective. The units of resource for the intervention will be collected directly and the use of other health care services by both groups will be collected through a patient questionnaire. Data on social care, other welfare services and employment details will be collected from the Patient Service Utilisation questionnaire. Intervention costs will be based on delivery costs within the trial and include supervision and appropriate capital and overhead amounts. Other unit costs will be based on long run opportunity costs and drawn from national sources. Full sensitivity analyses will be conducted with bootstrapping to provide confidence intervals around cost and effect estimates and to produce cost acceptability curves.

Qualitative data will be subject to content analysis within a qualitative methodological framework using QSR NVivo software and analysed according to the conceptual matrix of Miles and Huberman [39].

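### The only stated missing-data check, imputation by best subset regression, carries no imputation uncertainty as named; done as a single imputation at 20% loss it would misstate either the precision or the size of the effect

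*Protocol article*

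**What the plan says.** Under Statistical analysis of clinical data, the protocol article sets the primary analysis of four-month PHQ-9 as "between groups analysis of covariance on individual baseline depression score". It adds: "Analysis will take clustering into account by use of robust standard errors in Stata". Neither sentence mentions imputation.

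Missing data are then covered by one clause: "We will investigate the effects of any missing data using imputation by best subset regression". The article does not say how many imputations are made, whether a random residual is added, which predictors are candidates, or whether arm and practice are among them.

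The expected amount of missing data is given under Sample Size: "we will recruit and randomise 550 patients to anticipate a loss to follow up of 20" per cent, so that 440 are followed up.

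**The concern.** Imputation by a regression on a selected subset of predictors, taken as named, puts a predicted value where an outcome is missing. If the filled-in data set is then analysed once, the predictions count as observations. They lie on the fitted line and add apparent sample size without adding information.

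Choosing predictors by best subset raises a second problem, because arm may or may not be selected. If it is selected, the standard error is too small. If it is not, patients with imputed outcomes show no treatment difference, and the overall effect is diluted.

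This is the only check the article states on how attrition affects the result. It could confirm the primary result with false precision, or suggest that attrition matters when only the imputation model has pulled the estimate down. The clause refers to any missing data, so it may also reach the secondary outcomes and the twelve-month data.

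**Working it through.** **Inputs from the protocol article.** 48 practices (Recruitment of GP practices). From Sample Size: 550 recruited, 440 followed up, effect size 0.4 and ICC 0.06. The design effect stated there plays no part in this point.

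**The plan's own figure.** 440 / (1 − 0.20) = 550, as stated. The fraction observed is 440/550 = 0.80.

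**Single imputation, fitted values, arm in the model.** Suppose the predictors are those of the analysis of covariance (arm and baseline score).
- Every imputed residual is zero, so the regression coefficients equal the complete-case coefficients.
- The robust variance has the form B M B. Here M is built from the residuals, and B is the inverse of the cross-product matrix of the covariates.
- M is unchanged because the imputed residuals are zero. B shrinks by about 440/550 because it now uses 550 rows.
- The variance is therefore multiplied by 0.80 × 0.80 = 0.64 and the standard error by 0.80, which is 20% too small.
- A nominal 5% test would reject at about 2 × [1 − Φ(1.96 × 0.80)] = 11.7%.

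**Single imputation, fitted values, arm omitted.** Imputed patients contribute no arm difference, so the expected estimate is about 0.80 × 0.40 = 0.32.

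**Simulation.** 48 practices, 550 patients (550/48 = 11.5 per practice), ICC 0.06, true effect 0.40, outcomes missing completely at random, and analysis of covariance with practice-robust standard errors and t on 47 degrees of freedom. The article does not give the correlation of baseline with outcome, so 0.3 and 0.5 were assumed. At 0.5, an extra predictor with coefficient 0.5 was also tried. There were 2000 runs per scenario, except for multiple imputation (600). The true SE is the standard deviation of the estimates across runs.

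| Method | Mean estimate | Reported SE / true SE | 95% interval misses truth |
|---|---|---|---|
| Single, fitted value, arm in, 20% loss | 0.397 to 0.401 | 0.78 to 0.82 | 11.1 to 12.8% |
| Single, random residual added, arm in, 20% loss | 0.398 to 0.403 | 0.81 to 0.83 | 10.7 to 11.6% |
| Single, fitted value, arm omitted, 20% loss | 0.319 to 0.322 | 0.98 to 1.00 | 14.3 to 15.2% |
| Single, fitted value, arm in, 10% loss (correlation 0.5) | 0.397 | 0.91 | 7.7% |
| Multiple (20 sets, Rubin's rules), practices ignored, 20% loss (correlation 0.5) | 0.400 | 0.91 | 8.2% |
| Complete cases, 20% loss | – | 0.97 to 1.01 | – |

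The simulation agrees with the algebra. Adding one random residual hardly helps. Multiple imputation removes roughly half of the shortfall even when the imputation model ignores practices; what remains is a reason to account for practice.

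**The case against.** The strongest reply is that the article never says single. The number of imputations, residual draws, predictors and the rule for combining variances are details that a condensed article commonly leaves to an analysis plan, and that plan is not shown. This stands in part. Silence on those details is no fault in itself, and the size of the error can only be stated conditionally. But the article does positively name a method, and that method has no mechanism for imputation uncertainty unless one is added. An analysis plan that simply followed the text would inherit the weakness.

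Three stronger readings are tempting, and the document does not support them:
- **That the primary test has a type I error near 12%.** The sentences defining the primary analysis mention no imputation, and the imputation clause speaks of investigating effects. That reads as a sensitivity analysis. In the simulation, the complete-case analysis had a nearly correct standard error.
- **That the standard error will be 20% too small.** This holds for single imputation with arm in the model at 20% loss. At 10% loss the shortfall is about 9 to 10%. With arm omitted, the standard error is about right and the estimate is wrong instead.
- **That the check is worthless.** With arm and informative extra predictors in the model, even a single imputation can show whether the point estimate moves; its reported precision is what cannot be trusted. If only the covariates of the main analysis are used, the fitted-value estimate simply reproduces the complete-case one.

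**Conclusion.** The point holds as a conditional one of moderate severity, confined to the sensitivity analysis. Every single-imputation version examined misleads at 20% loss. With arm in the model, the standard error is 18 to 22% too small with fitted values and 17 to 19% too small with a random residual. With arm omitted, the effect is diluted by a fifth, from 0.40 to about 0.32. The article does not say whether arm is forced into the model, so which fault would arise is left open.

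These sizes assume that a single imputation is meant, that the planned 20% loss occurs, and that data are missing completely at random. They also rest on the assumed baseline-outcome correlations of 0.3 to 0.5, although the 0.80 ratio itself does not depend on the correlation or on the ICC. No defect in the primary analysis of covariance is shown.

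**What to change.** Replace the named method with multiple imputation combined by Rubin's rules, for example with 20 to 50 data sets. Arm and baseline PHQ-9 should always be in the imputation model and not subject to selection. Add the minimisation factors (centre, deprivation, practice size), the PHQ-9 from the other follow-up and predictors of missingness. Account for practice, for example by a practice random effect or by imputing within arm with practice effects. Then fit the same clustered analysis of covariance to each data set. State plainly that this is a sensitivity analysis to the primary result.

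If multiple imputation was intended all along, a sentence saying so, with arm and practice included, settles the point.

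The cost is a change of wording and a few hours of programming. The interval from the sensitivity analysis will be somewhat wider than under single imputation. Recruitment and data collection are untouched.

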### Frequency of analyses

We will analyse data at four and twelve months follow up. The DMEC will undertake an interim data analysis to detect any reason for halting the trial.

## Ethical Issues

We will conduct the trial is such a way as to protect the human rights and dignity of the participants as reflected in Helsinki Declaration [40]. Participants will not receive any financial inducement to participate. The study has received Multi-Centre Research Ethics Committee approval from the South West Research Ethics Committee in the UK. Local Research Ethics Committee and NHS Research and Development approvals have also been given for each recruitment site. To conform to data protection and freedom of information Acts, all data will be stored securely and anonymised wherever possible. No published material will contain patient identifiable information.

## Obtaining informed consent from participants

Informed consent will be determined by a two phase consent process. Participants will receive a study information sheet in the post and a form seeking their permission to be contacted by a member of the research team, not at this stage to give consent to trial participation. Full informed consent will only be obtained through an interview by a researcher where the information sheet is fully explained and where the opportunity to ask questions is given. The opportunity to withdraw from the trial will be fully explained. Researchers seeking consent will be fully trained and supervised by the CI and site leads. Communication and recording systems will be set up to enable the trial team to monitor and act on participants' wishes to withdraw from the trial.

## Risks and anticipated benefits for trial participants and society

All participants will receive usual GP care, and therefore no treatment will be withheld to participants in this trial. This trial may in fact benefit individual participants, since collaborative care is not routinely available and has been shown to be effective in our trial platform. By participating in this trial, participants will also receive a more intensive level of monitoring than that normally received in primary care.

## Informing potential participants of possible benefits and known risks

The patient information leaflets will provide potential participants with information about the possible benefits and any known risks of taking part in the trial. Participants will be given the opportunity to discuss this issue with either their GP or trial coordinator prior to consenting to participate. The trial coordinator will inform the participants if new information comes to light that may affect the participants' willingness to participate in the trial.

### Suicide

Inherent in the nature of the condition under scrutiny (depression) is the risk of suicide and deliberate self-harm. All participants will be subject to usual GP care, and the primary care physician will be responsible for the day to day management of depression - and will ultimately be responsible for all patient-level treatment/management decisions - including prescribing, referral and assessment of risk. The pragmatic nature of this trial means that we will not seek to influence this arrangement. However, we will follow good clinical practice in monitoring for suicide risk during all researcher encounters with trial participants. Where any risk to participants due to expressed thoughts of self-harm is encountered, case managers will apply the procedures taught in the STORM training [41], and all sites will follow a local suicide protocol. Systems will be put into place to ensure that the CI, trial coordinator and researchers will be informed should there be any risks to the participants' safety.

### Trial Steering Committee (TSC) and Data Monitoring and Ethics Committee (DMEC)

A Trial Steering Committee has been set up, in addition to a data monitoring and ethics committee (DMEC). These committees will meet at least annually. The DMEC will undertake an interim data analysis to detect any reason for halting the trial.

### Forecast execution dates

The preparatory period started in September 2008, and will continue for 9 months. Recruitment will begin in June 2009 for a period of 18 months. Follow up will last 15 months, at four (T1) and 12 months (T2) after inclusion (with an additional three months of back up built in). Data analysis and reporting will take another 6 months. The entire study period will last for 48 months.

## Discussion

The current trial is designed to implement evidence based treatments within the UK primary care setting. The multiple components of collaborative care for depression have been shown to improve outcomes for patients [11-13,42]. However despite a number of collaborative care models being currently trialled in Europe [43-45] the vast majority of the evidence emerges from the US, demanding the need to test a model that is specific to the UK context. Collaborative care is a complex intervention, the development of which ideally requires a phased approach [15,16,46]. Our trial utilises this phased approach, and follows on from a previous Phase II trial which demonstrated that the collaborative care intervention can be both effective and acceptable to patients [18,20]. We have designed this Phase III cluster trial to deal with contamination issues which we explored and identified in our Phase II trial: cluster-randomised trials are recommended for situations where systems level interventions such as collaborative care are to be tested [47] since patient-randomised trials may be vulnerable to contamination from the intervention to control patients.

The outcome of this trial will have implications for the NHS, in terms of helping to improve the organisation of its care for depressed patients in primary care. We expect the results to assist primary care healthcare providers to choose how to deliver an effective model of enhanced depression service.
